### Endpoints and variables

The primary endpoint will be the difference in mean days of hospital stay per year between patients included in the integrated and functional HC programs. Secondary endpoints will include the assessment of the differences between the two HC models i.e., mortality and hospital admissions, based on the IHI Triple Aim (Better Care, Better Health, Lower Costs) [26]. To this end, variables regarding subjects’ health status, quality of care, and resource utilization of patients included in the two models will be compared (Table 3). The demographic characteristics of the study participants will also be recorded.

**Table 3 Tab3:** Study variables

	Definition and Measurements	Categories
Demographic Characteristics		
Age	At the moment of entering the HC program	65–74 75–84 > 85
Gender		Male | Female
Health Status		
Caregiver	At the time of entering the HC program	Yes | No
Level of dependency	Scale defined by Royal Decree 174/2011; Law 39/2006 of Promotion of Personal Autonomy and Care for People in Situations of Dependency.	Grade I (25–49): Moderate dependency Grade II (50–74): Severe dependency Grade III (75–100): Great dependency
Decubitus ulcer	At physician’s discretion	Presence | absence
Drugs prescribed	By active substance.	Not polymedicated (< 5) Polymedicated (5–10) Hyperpolymedicated (> 10)
Comorbidity burden	Measured by Adjusted Morbidity Groups (GMA) risk assessment tool. GMA considers the type of disease (i.e. acute or chronic), number of systems affected, and complexity of each disease, which is coded by the International Classification of Diseases (ICD-9-CM) and stratify depending on the complexity.	31 qualitative ordinal GMA levels.
Mortality	Death during follow-up	Yes | No
Realization of CGA		Yes | No
Assessments included in CGA		
Performance of normal daily tasks	Barthel Scale [27]	Total dependency (< 20) Severe dependency (20–60) Moderate dependency (61–90) Mild dependency (91–99) Autonomous (100)
Mental health	Pfeiffer’s Test [28]	High risk (≤2) Mild cognitive impairment (3–4) Moderate cognitive impairment (5–7) Severe cognitive impairment
Decubitus ulceration risk	Braden Test [29]	High risk (< 12) Moderate risk (13–14) Low risk (15–18)
Social risk	TIRS [30]	There is social risk when one indicator over 6 is positive
Anxiety	Goldberg Scale [31]	Probable anxiety (≥4 positive responses) Probable depression (≥2 positive responses)
Geriatric depression scale	Yesavage Scale [32]	No depression (1) Possible depression (≥ 2)

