Mobility	Timed Up and Go Test [33]	Normal (< 10) Very little impaired (10–19) Moderately impaired (20–29) Severely impaired (≥30)
Comorbidity	Charlson Index [34]	No comorbidity (0–1) Low comorbidity burden (2) High comorbidity burden (> 3)
Social state	Social Scale [35]	No social risk (≤9) Social risk (10–14) Social problem (≥15)
Overburden of the caregiver	Zarit Test [25]	No overburden (< 46) Intense overburden (> 56)
Nutritional state evaluation	MNA [36]	Malnutrition (≤7) Malnutrition risk (8–11) Normal nutritional status (≥12)
Home adequacy	Revision of home adequacy to determine the need of social worker intervention	Social worker is recommended when at least one item is positive
Falls	Number of falls in the last year	–
Frailty	Gérontopôle Frailty Screening Tool [37]	Frailty identification if one item of the scale is positive.
Social services cost	Number and cost of social worker visits	–
Quality of life	EuroQOL 5D-3 L [24, 38, 39]	No problems (Level 1) Some problems (Level 2) Extreme problems (Level 3)
Quality of Care		
Physicians PQI	Prescription Quality Index of the physician [40]	Include assessment of three categories: More adequate therapeutic alternatives Hyper prescription of a particular group of drugs Selection indicators to promote safer and more effective alternatives available
Prescriptions	Number of prescription events per patient	–
Alternative drugs with therapeutic benefit	Percentage of use of the alternative drug as assessed by the physician	–
Shared Interdisciplinary Individual plan		Yes | No
Chronicity	Number of Complex Chronic Patients and Advanced Chronic Disease patients in the program	–
Satisfaction with health care received	IEXPAC Scale [23]	Satisfactory (=10) Unsatisfactory (< 10)
Overburden of the caregiver	Zarit Scale [25]	No overburden (< 46) Intense overburden (> 56)
Resource Utilization		
Family doctor visits	Number of at-home visits, other medical professional, primary care center or virtual appointments of the patient or the caregiver	–
Nursing staff visits	Number of at-home visits, other medical professional and primary care center appointments of the patient or the caregiver. Also, number of virtual consultations, including remote evaluation or by phone of medical record	–
Hospitalizations	Number of programmed, emergency and daycare admissions	–
Readmissions	Number of successive hospitalizations due to the same pathology in less than 30 days	–

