Admissions to other public health care centers	Number of admissions, including convalescence, subacute, long-lasting and palliative units	–
Hospitalizations per year	Days hospitalized	–
Intermediate resources	Number and cost of laboratory tests, Radiology and interconsultations	–
Pharmaceutical costs	Expenditure per patient and medical professional during a year	–
Hospitalization-at-home device use	Number of activations per year and total of hospitalization days	–
Social services intensity	Monthly hours spent by the social worker. Costs derived from teleassistance, cleaning and cooking aid, reused orthopedic material and family worker	–
Call to emergency services	Number of patient intervention requests per year.	–
Perception of healthcare professionals	Qualitative, self-administered questionnaire of difficulties in HC practice, based on the survey reported by Linares et al. [20]	

*CGA* Comprehensive Geriatric Assessment, *HC* Home Care

Particularly, the baseline health status of study subjects will include the Gerontôpole frailty screening tool and the Adjusted Morbidity Groups (GMA) risk assessment tool, which considers the type of disease, number of systems affected, and complexity of each one [21, 37]. Additionally, a complete baseline Comprehensive Geriatric Assessment (CGA) will be performed, including the following assessments: the ability to perform normal daily tasks (Barthel scale), mental health status (Pfeiffer test), decubitus ulceration risk (Braden test), social risk (TRIS), geriatric depression (Yesavage scale), mobility status (Timed up & go test), comorbidity burden (Charlson Comorbidity Index), nutritional state (Mini-nutritional Assessment), and social status (Table 3) [27–35, 41]. The health-related quality of life of study participants and satisfaction of caregiver will be assessed at baseline and at the final follow-up visit using the EuroQoL IEXPAC and Zarit questionnaires, respectively [23–25].

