### Statistical analysis

The sample size calculation was based on an incidence of hospital admission of 40% and a reduction of 10% in the study group, a 2-year follow-up, and a 1:1 ratio for control and intervention groups. Under these constrains, a fixed alpha and beta errors of 5%, yielded an estimated size of 581 subjects per group. The statistical power of this sample, assuming alpha and beta errors of 5% was 85.3%.

All collected variables will be described for the overall study sample and for both study groups. Quantitative variables will be described as the mean and standard deviation (SD), and as the median and interquartile range (IR) for normally- and non-normally distributed variables, as confirmed by the Kolmogorov-Smirnov test. Categorical variables will be described as frequencies and percentages. Measures of central tendency will be compared using the T-test for independent samples or ANOVA, or their non-parametric counterparts: the Mann-Whitney U and Kruskal-Wallis tests. Categorical variables will be compared using the Chi-square test or Fisher’s exact test. If post hoc analyses are performed, the Bonferroni or the Games-Howell adjustments will be applied. Variables with differences in the bivariate analysis at baseline (*p* < 0.1) and those considered clinically relevant for the authors will be included in a linear multiple logistic regression to build a multivariate model to predict the difference in mean days of hospital stay and costs of patients in the HC program. To address Better Care and Better Health endpoints, the authors will apply a binary logistic regression for mortality and hospital admission variables; age, gender, and comorbidity burden will be included as adjustment variables. A backward stepwise regression will be used to avoid overfitting of the model obtained.

A significance threshold will be set at two-sided alpha value < 0.05. The analysis will be performed with SPSS (IBM Corp. Released 2012. IBM SPSS Statistics for Windows, Version 21.0. Armonk, NY: IBM Corp.).

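### Table 3 leaves some scores without a category (Zarit 46–56, age 85, Charlson 3, Braden 12), mislabels the Pfeiffer test and splits IEXPAC at 10, and no baseline-adjusted analysis is specified for the repeated questionnaires

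*Protocol article*

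**What the plan says.** Table 3 (Protocol article, Endpoints and variables) gives each study variable a definition and, for most scales, a set of categories. The rows at issue are:

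- **Zarit**, listed under both Health Status and Quality of Care: "No overburden (< 46) Intense overburden (> 56".
- **Charlson:** "No comorbidity (0–1) Low comorbidity burden (2) High comorbidity burden (> 3".
- **Braden:** "High risk (< 12) Moderate risk (13–14", followed by a low-risk band from 15 to 18.
- **Age**, taken at entry to the home care programme: 65 to 74, 75 to 84, and above 85.
- **Pfeiffer:** "High risk (≤2) Mild cognitive impairment (3–4", then 5 to 7 as moderate, then a severe category with no number.
- **IEXPAC:** "Satisfactory (=10) Unsatisfactory (< 10".

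The same section says that the health status, quality of care and resource variables of the two models will be compared. It adds that quality of life and satisfaction "will be assessed at baseline and at the final follow-up visit using the EuroQoL IEXPAC and Zarit questionnaires".

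The Statistical analysis section gives general rules. "Measures of central tendency will be compared using the T-test for independent samples or ANOVA", or their non-parametric counterparts; categorical variables go to a chi-square or Fisher test. Regression models are named for hospital days and costs, and for mortality and hospital admission. The second pair is adjusted for age, gender and comorbidity burden.

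**The concern.** The article does not leave these categories to a later document. It fixes them, and some do not cover the scale. A caregiver scoring 50 on Zarit cannot be placed in a categorical comparison, and someone must then drop the case or invent a rule after seeing the data. The Pfeiffer row can mislead in another way: read literally, it puts the worst-sounding label on the best scores of a test that also decides eligibility and who completes the questionnaires. The IEXPAC split puts a score just under 10 in the same class as the lowest possible score.

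The second part concerns use of the data. Patients are not randomised and there is one centre per model, so the groups may already differ on these questionnaires at the start. The baseline values are collected, but the tests named for these scores make no stated use of them.

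**Working it through.** **1. Coverage of the bands.** Each whole-number score was checked against the printed limits.

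| Variable | Printed bands | Scores in no band |
|---|---|---|
| Zarit | <46; >56 | 46 to 56: 56 − 46 + 1 = 11 scores |
| Age | 65–74; 75–84; >85 | 85 |
| Charlson | 0–1; 2; >3 | 3 |
| Braden | <12; 13–14; 15–18 | 12 |
| Barthel, drugs prescribed, Timed Up and Go, Social Scale, MNA | as printed | none |

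The last row shows that gaps are not a convention of the table. The Zarit gap appears in both Zarit rows. Nothing is printed for Braden above 18 or Yesavage 0 either, but whether those scores can occur depends on scale ranges that the article does not give, so they are not counted here.

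**2. Pfeiffer.** Table 3 runs from high risk (2 or less) through mild (3–4) and moderate (5–7) to severe, so higher is worse. Study conduct defines cognitive impairment as 5 or more, and Selection criteria uses the same threshold. The label on the lowest band contradicts both its own row and those sections. The row implies that severe starts at 8, since moderate stops at 7, but no limit is stated.

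**3. IEXPAC.** There is no gap. The satisfactory class holds one value, 10, which appears to be the top score because no higher category is printed. The article does not state the scale range.

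**4. Which analyses reach the questionnaires.**

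| Outcome | Model named in Statistical analysis |
|---|---|
| Hospital days, costs | Regression with covariates |
| Mortality, hospital admission | Logistic regression with age, gender, comorbidity burden |
| EuroQoL, IEXPAC, Zarit | None; only the general two-group tests apply |

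**5. What baseline adjustment could be worth.** The article gives no correlation between baseline and final scores and no baseline gap. Assume r = 0.5, 0.6 or 0.7, equal spread at both visits, and a baseline gap of 0.2 SD. Relative to a comparison of final scores alone:

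| r | Residual variance, 1 − r² | Reduction | Equivalent extra patients, 1/(1 − r²) − 1 | Baseline gap carried over, r × 0.2 SD |
|---|---|---|---|---|
| 0.5 | 0.75 | 25% | 33% | 0.10 SD |
| 0.6 | 0.64 | 36% | 56% | 0.12 SD |
| 0.7 | 0.51 | 49% | 96% | 0.14 SD |

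If change scores were tested instead, the variance factor would be 2(1 − r) = 1.00, 0.80 or 0.60. Adjustment is still smaller at each r (0.75, 0.64, 0.51).

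**The case against.** Four points on the other side have force.

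- **The text does not say that baseline is ignored.** A reader might infer that two-year scores will be compared without their baseline value. The article assigns no test to these questionnaires, and a t-test or Mann-Whitney test could be run on change scores. It is a condensed article and a fuller plan may exist. What stands is narrower: the only tests that reach these scores are unadjusted, and no baseline-adjusted analysis is specified.
- **Patients need not drop out of the models.** A reader might infer that people aged 85 or with Charlson 3 are lost from the regressions. The article does not say that age enters in bands, and it describes and compares quantitative variables as numbers. The comorbidity burden row of Table 3 is measured by GMA, not Charlson. The age gap reaches the adjusted models only if bands are used. The Charlson, Braden and Pfeiffer faults mainly affect baseline description.
- **Age at programme entry is a stated definition.** It may look like an error because enrolment has a minimum of three months and no stated maximum. The article does not say how long patients have been enrolled, so no error is shown.
- **Adjustment is not free.** Study baseline falls at least three months after programme entry. Conditioning on a score measured after the care model began can remove benefit already gained, and it does not remove unmeasured confounding. The r × gap figure treats the baseline gap as pure confounding with a correct slope.

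The objection leaves the gaps, the Pfeiffer label and the IEXPAC split untouched.

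**Conclusion.** The table faults are certain on the face of the text: 11 Zarit scores and one value each of age, Charlson and Braden have no category; the Pfeiffer label runs against the protocol's own threshold, with no limit for severe; and IEXPAC is reduced to 10 or not 10. Zarit is the most important, because it is a repeated measure and the unclassified range is everything between no overburden and intense overburden.

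The missing baseline-adjusted analysis is a worthwhile improvement to a non-randomised comparison, not a proven error. Its size depends on assumed values: a 25% to 49% cut in residual variance for r from 0.5 to 0.7, and 0.10 to 0.14 SD of carried-over difference for a 0.2 SD baseline gap. Neither r nor the gap comes from the article. That 10 is the IEXPAC maximum is inferred.

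The primary endpoint is untouched, and the mortality and admission models are affected only if age enters in bands. The point should be corrected, but it does not threaten the main result.

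**What to change.** 1. Close the bands in Table 3: give Zarit 46–56 its own band in both rows, change the top age band to 85 and over, make the top Charlson band 3 and over, and assign Braden 12.
2. Correct the label on the lowest Pfeiffer band and state the limit for severe.
3. Keep all bands for description only, and analyse Zarit, IEXPAC and age as numeric values.
4. For each two-year questionnaire outcome, fit the final score on study group, baseline score and a fixed covariate set; age, gender and comorbidity burden are already named for the other secondary outcomes.
5. State with that analysis that baseline follows at least three months in the care model, so the adjusted difference may leave out benefit already gained, and that unmeasured confounding remains. Showing the unadjusted difference beside it lets the reader see what the adjustment does.

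The cost is a table correction and a few sentences of analysis text, settled before the two-year scores are analysed. No new data are needed. The only real downside is the one in step 5.

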Catalonia is the most north-eastern region of Spain, with a population of over 7.5 million people, 19% of which is older than 65 years. Here, HC programs are highly implemented, with nearly 90% of primary care units using traditionally integrated HC approaches within each provision of healthcare service, that enroll a 5% of the population older than 65 years. However, a survey of primary care professionals involved in HC programs revealed important disadvantages of this model, such as a high burden of care, time constraints, low resources and lack of coordination with other levels of care as each of the services provides HC assistance besides their center-based duties [20]. The change from a traditional integrated HC model to a functional full-time HC is expected to result in better outcomes for patients (clinical and related to the attendance experience), increased satisfaction for the professionals involved, and less use of healthcare resources. However, there is little or no evidence regarding the benefits and drawbacks of the two models when operating in the same healthcare environment. This study aims to compare two HC programs for older people applied in Catalonia: a traditional integrated HC model provided by healthcare professionals of primary care units and a specific full-time unit of medical professionals based on a functional HC model.

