## Methods

### Study design

This quasi-experimental study will compare the outcome of two HC models implemented in two primary care centers in Badalona (Barcelona, Spain). The control group will consist of patients following the integrated HC model, provided by the primary care center *Gran Sol*, and the study group will consist of patients following the new HC model (hereinafter, functional HC model), linked to the primary care center *Apenins*. Both HC teams consist of a general practitioner and a nurse. In the integrated model, HC is given by the same healthcare team providing medical care at the primary care unit with an average of 1500 inhabitants assigned to each team. By contrast, in the functional model, HC is given by a healthcare team specifically trained in the management of older, frail and multimorbid patients, providing only full-time preventive home visits and connecting to other further required special provision services. Further details regarding the characteristics of each model are shown in Table 1. The rationale for choosing these two centers relates to the balanced demographic characteristics of the reference population (Table 2).

**Table 1 Tab1:** Main characteristics of the two investigated models

Integrated HC		Functional HC
Characteristics of the healthcare team		
**Team composition**	Nurse and family doctor.	
**Team function**	The same healthcare team provides HC and manages patients in the primary care center.	The healthcare team is dedicated exclusively to HC.
**Interprofessional communication**	Healthcare professionals are part of the healthcare team regularly managing patients in the primary care center.	Although not managing patients in the primary care center, the HC team is part of the health care staff of the center and their members participate in the center meetings as specialists.
**Training**	• Regular training of family doctors, including regular stays at mental health and geriatrics units. • Regular training of nurses.	• Regular training of family doctors, including regular stays at mental health and geriatrics units. • Nursing staff receives additional training regarding the management of chronic patients, fragility, and palliative care.
**Type of professional in each visit**	Nurse, family doctor or both	
Services and visit schedule		

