On the other hand, some limitations can be predicted. Firstly, a possible Hawthorne effect, according to which the quality of care may improve due to the fact that healthcare professionals are being assessed [47] cannot be ruled out. To our understanding, this effect —in case it occurs— is likely to decline throughout follow-up. Secondly, it seems almost unavoidable that patients will fail to report the use of private facilities, a fact that shall be considered at the moment of reporting results. Finally, this study has a risk of unbalanced reporting bias due to the differences in the healthcare teams of each model. Specifically, whereas in the integrated HC group multiple observers will contribute to data capture, in the functional group all assessments will be performed by a single HC team. In this regard, the reporting bias is likely to be attenuated in the integrated group by the presence of multiple observers, but not in the functional group. To increase homogeneity in practices and data recording, all investigators will receive a brief training.

In summary, the proposed study will permit assessment of health outcomes, feasibility, and resource utilization of new functional HC model and identify its strengths and weaknesses compared to the integrated model. The results obtained from this study may have important policy implications.

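### Prescribing quality is defined per physician, so one home-care-only doctor is set against about 13 doctors whose lists lie mostly outside the study

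*Protocol article*

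**What the plan says.** Under Endpoints and variables, the protocol article says that variables on "quality of care, and resource utilization of patients included in the two models will be compared", and points to Table 3 for the list. The Quality of Care block of that table opens with the "Prescription Quality Index of the physician", built from three categories: more adequate alternatives, hyperprescription of a drug group, and safer or more effective alternatives. The next row is the "Number of prescription events per patient", so the table itself distinguishes a physician-level from a patient-level quantity. Under Resource Utilization, pharmaceutical cost is the "Expenditure per patient and medical professional during a year".

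Study design says that "Both HC teams consist of a general practitioner and a nurse". Integrated teams also manage patients at the centre, "with an average of 1500 inhabitants assigned to each team". Table 1 says the functional team does home care exclusively. The limitations in the Discussion add that "in the functional group all assessments will be performed by a single HC team", whereas the integrated group has multiple observers.

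**The concern.** The stated aim concerns the care received by patients in each model, but the variable is a property of the doctor. The two kinds of doctor have different lists: an integrated doctor prescribes for everyone assigned to the team, and the functional doctor only for home-care patients. At least the hyperprescription category plausibly depends on age and morbidity. A difference in the index could then come from who is on the list rather than from how home care is organised.

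The second problem is the number of units. One doctor stands for the whole functional arm, so that doctor's habits cannot be told apart from the effect of the model. What is at stake is the interpretation of one secondary Quality of Care variable, and of the per-professional part of pharmaceutical expenditure.

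**Working it through.** The article gives no figure for the number of physicians or for the index, so there is no stated result to reproduce. The sizes below are derived.

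**Inputs**
- Reference population of the integrated centre: 19,442, of whom 3,480 are aged 65 or over (Table 2).
- Average inhabitants per integrated team: 1,500, with one general practitioner per team (Study design).
- Home-care enrolment: programmes in Catalonia "that enroll a 5% of the population older than 65 years" (Background). This is a regional rate, not a figure for the centre.
- Planned subjects per group: 581 (Statistical analysis), used as an upper bound on study patients.
- Functional teams: one (Discussion).

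**Number of integrated doctors**
- 19,442 / 1,500 = 12.96, about 13.
- If the average list were 1,200 to 1,800 (an assumed range), the count would be 16.2 to 10.8.

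**Share of an integrated list that is in the study, by headcount**
- Low: 0.05 × 3,480 = 174 patients. 174 / 12.96 = 13.4 per doctor. 13.4 / 1,500 = 0.9%.
- High: 581 / 12.96 = 44.8 per doctor. 44.8 / 1,500 = 3.0%.
- So 97% to 99% of the people on the list are outside the study. Also, 1 − 3,480 / 19,442 = 82% of the reference population is under 65.

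**Share by prescribing volume**

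Headcount understates the weight of home-care patients in a prescribing index. If a study patient receives k times the prescribing of other patients and f is the headcount share, the prescribing share is fk / (fk + 1 − f). The values of k are assumptions, because the article gives none.

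| Study patients | f | k = 5 | k = 10 |
|---|---|---|---|
| 174 | 0.9% | 4% | 8% |
| 581 | 3.0% | 13% | 24% |

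In every case shown, most of the prescribing behind the integrated index comes from people outside the study.

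**Test with the physician as the unit (1 v 13)**
- The single functional value can take any of 14 ranks. The smallest two-sided exact p for a rank test is 2/14 = 0.143.
- With 16 integrated doctors it is 2/17 = 0.118, and with 11 it is 2/12 = 0.167. A value below 0.05 would need at least 40 integrated doctors (2/41 = 0.049).
- A pooled t-test can be computed with one observation in an arm, but all of its variance comes from the integrated doctors. It asks whether this doctor is unusual among them. It cannot say whether the model is the reason.

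**Test with the doctor's value copied to each patient**

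The functional arm then has zero variance and the test treats repeated values as independent. I simulated no difference between models, with normally distributed doctor indices, 11 to 16 integrated doctors and a t-test on the copied values. The test was significant at 0.05 in about 89% to 90% of runs with 174 patients per arm and about 94% to 95% with 581. The article does not say that values will be copied. This only shows why that route is no remedy.

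**The case against.** The strongest objection is that the article never states the denominator of the index. It cites a source for the definition, and the sentence introducing Table 3 speaks of patients included in the two models. If the index were computed only on study patients, the case-mix argument would fall away. Operational detail of a secondary variable is also often left to a fuller document. This stands as a limit on certainty. It does not remove the point, because the wording in Table 3 assigns the index to the physician and contrasts it with a per-patient row. The single functional doctor would remain under either denominator.

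Several stronger readings are tempting and are not supported:
- A reader might call this a headline Better Care measure. It is one of seven Quality of Care rows. The article names mortality and hospital admissions as secondary endpoints and ties its Better Care and Better Health models to those two.
- A reader might infer that about 99% of the integrated index is about other people. That is a headcount from a regional rate. The range is 97% to 99% by headcount, and lower by prescribing volume.
- A reader might conclude that any difference mainly reflects age and morbidity. Two of the three categories concern choice between alternatives, and nothing in the article shows how far case mix drives them. The confounding is structural and its size is unknown.
- A reader might extend the criticism to all pharmaceutical costs. That row already lists expenditure per patient, so only the per-professional part is affected.

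It is also fair to say that the article names no specific test for this index, only general rules, and that descriptive reporting is compatible with them. Finally, moving to patient level does not by itself cure the single-doctor problem, so the fix must say so.

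**Conclusion.** The point holds on the plain reading of Table 3. A physician-level index does not measure what the article says will be compared. It would cover whole lists in one arm (study patients 0.9% to 3.0% by headcount) and home-care patients only in the other. It would rest on one doctor against about 13, where a rank test has a smallest two-sided exact p of 0.143. Case mix and model are confounded, and doctor and model cannot be separated in the functional arm.

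This rests on four assumptions: the index covers the doctor's whole list, the average list of 1,500 applies across the integrated centre, every integrated team contributes patients, and either the regional 5% or the planned 581 bounds enrolment. If the first fails, the case-mix part goes and the one-doctor part stays. The primary endpoint is not touched. This is a cheap improvement, not a threat to the study's main conclusion.

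**What to change.** - Define the three index categories on the prescriptions of enrolled study patients only, in the same way in both arms, and compare them at patient level with adjustment for age and GMA, which are both already recorded.
- State that patients are clustered by physician and that, with a single functional team, the effect of the physician cannot be separated from that of the model. Interpret any difference accordingly.
- Report the routine physician-level index, and the per-professional part of pharmaceutical expenditure, as description without a test. Compare the per-patient expenditure that Table 3 already lists.

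The cost is an additional query on prescription data, assuming that the indicators can be derived per patient from the records, which the article does not confirm. The restricted indicator will no longer match the routine physician-level index, so comparison with routinely published values is lost.
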